### Randomization

Computer generated list of random numbers using permuted block randomization will be created and uploaded in RedCap data base.When all the screening results are available and within the normal range, the patient will be randomly allocated in a ratio of 1:1:1 to one of the treatment groups. The study sites will be required to ensure inclusion and exclusion criteria for each patient prior to enrolment and enter the data in the baseline case report form with the eligibility criteria in RedCap data base. Upon verification of the case report form and the eligibility criteria, the ICMR-NIRT statisticians (randomization team) will approve for randomization and site investigators can proceed for online randomization in Redcap.

 Allocation concealment will be ensured, as the randomization team will not approve the randomization until the patient has been recruited into the trial, which takes place after all baseline assessments are completed. The intervention will be administered by the site investigators who will also be treating physicians.

### Treatment allocation

#### Arm 1 (intensified ATT with aspirin)

Participants in this arm will receive a high dose of rifampicin 25 mg/kg once daily and moxifloxacin (400 mg once daily) along with isoniazid and pyrazinamide for 2 months. Steroids will be administered to participants with MRC grades 1 and 2 for a duration of 6 weeks, while participants in grade 3 will be treated for 8 weeks. This regimen will also be intensified with 150 mg of aspirin once daily. Intensive phase will be followed by standard doses of rifampicin, isoniazid, and pyrazinamide for the next 4 months in the continuation phase (Fig. 1).

**Fig. 1 Fig1:**
[figure not shown]
Study schema

#### Arm 2 (intensified ATT without aspirin)

Participants in this arm will receive intensified ATT regimen and steroids like arm 1 but without aspirin in the intensive phase and standard doses of isoniazid, rifampicin, and pyrazinamide for the next 4 months in the continuation phase.

#### Arm 3 (control arm)

The control arm will receive treatment according to the standard national guidelines for TBM. They will receive a first-line regimen consisting of 2 months of isoniazid, rifampicin, ethambutol, and pyrazinamide followed by 10 months of isoniazid, rifampicin, and ethambutol daily in a fixed-dose combination (FDC) as per the various weight bands in National TB Elimination Programme of India. Participants will also receive steroids as in the other two arms.

### Recruitment

It is estimated that each collaborating institutes treat 80–120 patients with TBM each year. Our study team will work with departments of emergency medicine, internal medicine, and neurology. Any patient with symptoms and signs suggestive of TBM and undergoing lumbar puncture will be pre-screened for the trial after obtaining written informed consent. During pre-screening, CSF collected will be sent for gram staining, bacterial culture and sensitivity, AFB smear, MGIT, Gene Xpert/Xpert Ultra, Truenat, and any other laboratory studies as per the treating clinician’s advice. Once the patient is found to be diagnosed with TBM after pre-screening, screening assessments will be done after obtaining written informed consent explaining the details of the trial with participant information sheet. Written informed consent will be taken by the trial nurse. Participants information sheet and informed consent has been given as Additional file 2.

### Participant timelines and follow-up

In this assessment, demographic details, medical history, clinical examination, neurological assessment including Modified Rankin Score (MRS) and Glasgow Coma Scale (GCS), sociological assessment for compliance to trial procedures, and all other study procedures will be done. Blood will be collected for hematological (complete blood count—CBC) and biochemical tests (sugar, HbA1C, liver, and renal function tests), HBsAg, and HIV. Patients will also undergo CT or MRI imaging of the brain. We will also collect sputum for CBNAAT and AFB culture and do chest X-ray to rule out pulmonary TB. All eligible patients will be enrolled into the trial. At the time of enrolment, blood will be collected for immunological biomarkers (CRP, TNF-α, monocyte and dendritic cell functions, and other cytokines).

During the study period, patients will be followed as per the study schedule attached (Table 1). After admission to the study and treatment allocation, participants will be followed up every week for the first 2 months and monthly till the completion of the treatment. They will undergo clinical examination including detailed neurological examination and adverse event (AE) monitoring. After treatment completion, all participants will be followed up once in 3 months for a period of 12 months. Participants in the study arms I and II will complete 12 months of post-treatment follow-up at the 18th month study visit and participants in the control arm will complete their post-treatment follow-up at the 24th month study visit.

**Table 1 Tab1:** Study schedule

S No	Investigations	Pre-screening	Screening	Enrolment	W1	W2	W3	W4	W5	W6	W7	W8	M3	M4	M5	M6	M7	M8	M9	M10	M11	M12	M15	M^a^18	M21	M24
1	Screening consent		✓																							
2	Assess eligibility		✓	✓																						
3	Informed consent			✓																						
4	History and clinical examination		✓	✓	✓	✓	✓	✓	✓	✓	✓	✓	✓	✓	✓	✓	✓	✓	✓	✓	✓	✓	✓	✓	✓	✓
5	GCS		✓	✓	✓	✓	✓	✓	✓	✓	✓	✓	✓	✓	✓	✓			✓			✓	✓	✓	✓	✓
6	Modified Rankin’s score		✓	✓	✓			✓				✓		✓		✓			✓			✓	✓	✓	✓	✓
7	Sputum smear and MGIT^b^		✓																			✓		✓		
8	CSF analysis for AFB smear, MGIT, Xpert, and to rule out other etiology as appropriate	✓																								
19	CSF cytology, biochemistry,	✓																								
10	HIV		✓																							
11	Urine pregnancy test^c^		✓					✓				✓	✓	✓	✓	✓	✓	✓	✓	✓	✓	✓				
12	Hepatitis B and C		✓																							
13	LFT		✓			✓		✓		✓		✓		✓		✓			✓			✓				
14	RFT		✓			✓		✓		✓		✓		✓		✓			✓			✓				
15	Uric acid					✓		✓		✓		✓		✓		✓										
16	HbA1C (only for diabetics)		✓										✓			✓			✓			✓				
17	Hematology		✓					✓				✓				✓			✓			✓				
18	CD4 count if HIV positive		✓					✓				✓				✓			✓			✓				
19	Imaging (CT/MRI)		✓													✓										
20	CXR^b^		✓																							
21	ECG in 12 leads		✓					✓				✓				✓										
22	Intensive PK Serum^d^					✓																				
23	Sparse PK Serum					✓		✓				✓														
24	CSF PK (single time point)^d^																									
25	Adverse event assessment			✓		✓	✓	✓	✓	✓	✓	✓	✓	✓	✓	✓	✓	✓	✓	✓	✓	✓				
26	Storage of plasma and serum sample		✓					✓				✓				✓			✓			✓				
27	Neurological assessment			✓	✓	✓	✓	✓	✓	✓	✓	✓				✓			✓			✓		✓		✓
28	Quality of life assessment			✓												✓						✓		✓		✓

^a^Participants in the intervention arm will complete 12 months of post-treatment follow-up at 18th month study visit and participants in the control arm will complete their post-treatment follow up at 24th month study visit

^b^At baseline and when symptomatic

^c^Urine pregnancy test in women with reproductive potential

^d^Intensive PK serum and CSF to be planned between weeks 1 and 2

### Pharmacokinetics study

A full pharmacokinetic (PK) study of ATT will be carried out in 15 patients per arm per site in two sites any time between first and second week study visits. On the day of PK, the patient will be requested to be on an empty stomach. A sample of blood (2 ml) will be collected (0 h). The study drugs will be administered under direct supervision and the time of drug administration will be noted. Thereafter, 2 ml of blood will be collected at 2, 4, 6, 8, and 12 h. A single CSF sample for PK (preferably 2nd hour after ATT administration) will be also be collected. The same patients will undergo a sparse plasma PK (0, 2, and 4 h) at the end of the fourth and eighth week.

### Patient compliance

The drugs will be administered under supervision (except on Sundays) to ensure compliance. The importance of adherence to the treatment schedule will be reinforced at each visit. The cause for non-adherence will be identified. If the patient misses drug doses in the intensive phase (IP), it will be compensated at the end of the intensive phase. The compensation will be given for a maximum period of 15 days to complete 60 doses of the assigned regimen in the IP. Similarly, the missed doses in the continuation phase (CP) will be compensated at the end of CP so as to complete 120 doses in CP. Patients who do not attend treatment continuously for more than a month will be considered as lost to follow-up. For these patients, a minimum of two rounds of three attempts to contact them (telephonic/home visit) will be made. If these attempts are unsuccessful, then the participant will be considered lost to follow-up.

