The causes of mortality and morbidity in TBM are multifactorial, complicated by delayed presentations and poor diagnostic tests. The drug therapy used for TBM in adults and children also has significant limitations. The Infectious Disease Society of America, the American Thoracic Society, and the Centers for Disease Control and Prevention advise a regimen with 2-month intensive phase consisting of isoniazid, rifampicin, pyrazinamide, and ethambutol (HRZE) followed by 7 to 10 months of rifampicin and isoniazid (HR) in the continuation phase [12]. WHO recommends a 12-month regimen with 2 months of isoniazid, rifampicin, pyrazinamide, and ethambutol followed by 10 months of isoniazid and rifampicin in adults. The recent guidelines update supports a 6-month intensive regimen containing ethionamide (6HRZEto) for children and adolescents with TBM without evidence or suspicion of drug resistant tuberculosis (DRTB) [13]. Given the scarcity of available evidence concerning the optimal selection, dosage, and duration of antituberculous treatment (ATT), multiple regimens of varying duration are also being practiced. Additionally, the number of drugs administered differ during both the intensive and continuation phases. In addition to anti-TB drugs, there is also considerable variation in practice regarding the dose and duration of adjuvant therapy with corticosteroids and aspirin.

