### Sample size

The trial is powered to assess the superiority of intensified regimen (arm 1) compared to control regimen (arm 3). A systematic review and meta-analysis on treatment outcomes in TBM done by Stadelman et al. reported the proportion of mortality and disability after treatment is 24% and 32%, respectively [7]. The proportion of composite outcome (death or disability) is 56%. We assume a 20% reduction of composite outcome with our intervention (i.e., from 56 to 36%). We used the formula for Z test for comparing proportion between two groups (arm 1 and arm 3). Hence, to study the impact of “Intervention” compared to “Standard care” in reducing the composite outcome (death or disability), expecting a minimum difference of 20% between intervention arm with aspirin (arm 1) and control arm (arm 3), assuming 85% power of the study, 5% level of significance, 2-sided significance test; the required sample size was 112 patients in each arm. Considering 10% lost to follow-up, the total sample size was calculated as 372 with 124 in each arm. Previous clinical trials in TBM have evaluated mortality as an outcome and considered 30% reduction [14]. Since we propose to evaluate composite outcome of death or disability, we have assumed a conservative effect size of 20% reduction. The 10% loss to follow-up is assumed based on the previous TBM trials as well as randomized controlled trials conducted at ICMR-NIRT, Chennai [20, 21].

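### The missed-dose rule sets one continuation-phase target of 120 doses for all arms, which is only about 40% of the control arm's 10-month daily phase

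*Protocol article*

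**What the plan says.** The Patient compliance section gives two completion targets for patients who miss doses. For the intensive phase, make-up dosing runs for at most 15 days "to complete 60 doses of the assigned regimen in the IP". The next sentence extends the rule to the later phase: "the missed doses in the continuation phase (CP) will be compensated at the end of CP so as to complete 120 doses in CP". Neither sentence is limited to an arm.

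The Treatment allocation section gives all three arms a 2-month intensive phase, but what follows differs:

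- Arm 1: "standard doses of rifampicin, isoniazid, and pyrazinamide for the next 4 months in the continuation phase".
- Arm 2: "standard doses of isoniazid, rifampicin, and pyrazinamide for the next 4 months in the continuation phase".
- Arm 3 (control): "followed by 10 months of isoniazid, rifampicin, and ethambutol daily".

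The Participant timelines and follow-up section agrees with a 12-month control course. It adds 12 months of follow-up after treatment, and "participants in the control arm will complete their post-treatment follow-up at the 24th month study visit". No section gives a different continuation-phase dose count for control.

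**The concern.** A single dose target works only if the phase has the same length in every arm. That is true of the intensive phase and false of the continuation phase, which is 2.5 times as long in control (10 months against 4). A target of 120 is therefore complete treatment in arms 1 and 2, but less than half of the phase in control.

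What is at stake is equal enforcement of adherence. The Sample size section powers the trial on arm 1 against arm 3. The trial is open label, and under Randomization the site investigators who give the treatment are also the treating physicians. A site that takes the number at face value would chase missed doses in arms 1 and 2 and have no numerical reason to do so in most control patients. Any such difference could only lower drug exposure in control. If those doses matter to outcome, this favours the intervention in a superiority trial.

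**Working it through.** **Inputs**

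- Intensive-phase target: 60 doses (Patient compliance), over 2 months in every arm (Treatment allocation).
- Continuation-phase target: 120 doses, no arm named (Patient compliance).
- Continuation-phase length: 4 months in arms 1 and 2; 10 months daily in control (Treatment allocation).
- Planned patients: 124 per arm, 372 in total (Sample size).

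**Step 1: the protocol's dose rate.** 60 doses / 2 months = 30 doses a month.

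**Step 2: reproduce the stated figure.** Arms 1 and 2: 4 months × 30 = 120 doses. This matches exactly.

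**Step 3: apply the same rate to control.** 10 months × 30 = 300 doses, and 120 / 300 = 40%. Over the whole course, the stated targets add to 60 + 120 = 180 doses, against 60 + 300 = 360 for 12 months: 180 / 360 = 50%.

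**Step 4: does another day-count rescue the figure?** Supervised dosing excludes Sundays, so the counting basis has to be checked. A calendar month is taken as 365.25 / 12 = 30.44 days.

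| Basis | 2 months | 4 months | 10 months | 120 as share of 10 months |
|---|---|---|---|---|
| 30 doses a month | 60 | 120 | 300 | 40.0% |
| Calendar months, 7 days a week | 60.9 | 121.8 | 304.4 | 39.4% |
| 28-day months | 56 | 112 | 280 | 42.9% |
| Calendar months, 6 days a week | 52.2 | 104.4 | 260.9 | 46.0% |

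The stated 60 and 120 fit a 7-day count and not a 6-day count, so Sundays appear to be unsupervised dosing days. No basis makes 120 right for a 10-month phase.

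**Step 5: what the rule does if followed literally.** Take two illustrative patients who each miss 20% of the continuation phase; the 20% is an assumption for illustration.

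- Arm 1: 0.20 × 120 = 24 missed, 96 taken. The target is 120, so 24 doses are owed.
- Control: 0.20 × 300 = 60 missed, 240 taken. The target of 120 is already exceeded, so none are owed.

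A control patient falls short of the target only after missing more than 300 − 120 = 180 doses, that is 180 / 300 = 60% of the phase.

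**Step 6: who is covered.** One arm of three, 124 / 372 = 33% of planned patients. Within that arm, only those who miss continuation doses could be affected, and the article gives no figure for them.

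**The case against.** The best defence is that the number is correct for the phase it was written for. In the regimen descriptions the term continuation phase appears only for arms 1 and 2, and the control paragraph gives months and drugs without using it. On that reading the 120-dose rule never applied to control. The article also condenses a full protocol (version 1.3) that may hold arm-specific counts.

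The author probably did have the short regimens in mind, but the text does not say so. The preceding sentence refers to the assigned regimen, which covers every arm, and the next one carries the rule forward by analogy. Nor is the term reserved for the short regimens: the Background uses it for a standard regimen, "followed by 7 to 10 months of rifampicin and isoniazid (HR) in the continuation phase". That passage describes outside guidance and does not define this trial's terms, so it is supporting evidence only. If control is excluded, it is left with no continuation-phase target at all, and the same clarification is needed. The condensed-article argument would excuse a missing detail. Here a specific number is printed without restriction and conflicts with the control regimen.

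Part of the objection stands:

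- Control's course is fixed correctly elsewhere at 10 months daily after the intensive phase.
- The main clause of the rule still says that missed doses are made up, with no exemption for control.
- A daily-dosed control patient passes 120 about four months into the phase, so a sensible site is unlikely to treat it as the end of treatment.
- More than a month of continuous non-attendance already counts as loss to follow-up.

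These points limit the likely harm. They do not make the number right.

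**Conclusion.** The concern holds. The continuation-phase target is correct for arms 1 and 2 and wrong as written for control, where 120 doses is 40% of the phase at the protocol's own rate and 39% to 46% across the other day-counts. This rests on reading the compliance rule as covering all three arms, which is its plain wording, and on 30 doses a month, which both stated targets support.

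The 40% measures the gap in the rule; it does not estimate treatment lost or bias. The article gives no basis for estimating either. The intention-to-treat population, alpha and sample size are untouched. So is the per-protocol definition: its 80% threshold refers to prescribed treatment, which is each arm's own regimen (0.80 × 360 = 288 doses for control). The error is confined to the make-up target, but it falls on one side of the powered comparison and is worth correcting.

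**What to change.** State the continuation-phase make-up target by arm in the Patient compliance section: 120 doses for arms 1 and 2, and about 300 doses (10 months daily) for arm 3. If the sponsor does not count Sunday doses, the control figure would be about 261, but the 60 and 120 would then have to change too (to about 52 and 104), so the basis should be stated once. The 60-dose intensive-phase target can stay for all arms, and the per-protocol definition needs no change.

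The cost is one clause in the protocol and matching wording on the adherence form, with no added visits, procedures or patients. The Trial status section reports that recruitment had not begun when the article was written.

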### Concomitant medications

Concomitant antibiotic treatments of any kind are discouraged during the period of study drug administration unless absolutely indicated. During the course of the trial, a short course (< 2 weeks) of antimicrobial therapy may be permitted for concurrent illnesses. Short courses of antibiotic therapy (< 2 weeks) with drugs not indicated for the treatment of TB will be limited and the illness for which they are prescribed will be recorded. The following agents used to treat M. tb infections will not be used during the trial: streptomycin, thiacetazone, PAS, dapsone, amoxicillin clavulanic acid/clavulanate, clofazimine, capreomycin, any oxazolidinone antibiotic (e.g., linezolid), ofloxacin, levofloxacin, bedaquiline, pretomanind, and delamanid.

### Adverse event (AE) management

The participants will be closely monitored during the scheduled study visits. AEs will be collected from the initiation of treatment regimen onwards. All serious adverse events (SAEs) occurring during the trial period must be reported to the Institutional Ethics Committee (IEC) i.e., within 24 h of the investigator becoming aware of the event. They will also be reported to the sponsor and the competent authorities within the specified period of time as defined in New Drugs and Clinical trials Act 2019. The AEs will be graded as per DAIDS grading Table 2017 and managed as per protocol especially for grade III and grade IV events, hepatotoxicity, and cardiovascular system events [19].

### Criteria for discontinuing interventions

*Grade 2 toxicities:* For grade 2 toxicities, the patient will be followed more carefully, with additional laboratory and/or clinic visits as necessary, and the study drugs temporarily held at the investigator's discretion.

*Grade 3 toxicities:* For any grade 3 toxicity that in the investigator’s judgment is due to study drug(s), the causative study drug(s) will be held. The clinician will rule out other possible causes of the symptoms before discontinuing study medication. When possible, concomitant medications will be held first at the discretion of the investigator if he/she suspects they are contributing to the toxicity. Depending on the nature and severity of the toxicity, the degree to which it resolves, and/or the emergence of alternative explanations for the toxicity or the participant’s deterioration, the study drugs(s) may be restarted at the discretion of the investigator.

*Grade 4 toxicities:* Study drug will be permanently discontinued in any participant with grade 4 renal, hepatic, cardiac, or hematological toxicity.

For all toxicities that are treatment-emergent and require the study therapy to be temporarily or permanently discontinued, relevant clinical and laboratory tests will be obtained as clinically indicated and repeated as needed until final resolution or stabilization of the toxicity.

### Sample size

The trial is powered to assess the superiority of intensified regimen (arm 1) compared to control regimen (arm 3). A systematic review and meta-analysis on treatment outcomes in TBM done by Stadelman et al. reported the proportion of mortality and disability after treatment is 24% and 32%, respectively [7]. The proportion of composite outcome (death or disability) is 56%. We assume a 20% reduction of composite outcome with our intervention (i.e., from 56 to 36%). We used the formula for Z test for comparing proportion between two groups (arm 1 and arm 3). Hence, to study the impact of “Intervention” compared to “Standard care” in reducing the composite outcome (death or disability), expecting a minimum difference of 20% between intervention arm with aspirin (arm 1) and control arm (arm 3), assuming 85% power of the study, 5% level of significance, 2-sided significance test; the required sample size was 112 patients in each arm. Considering 10% lost to follow-up, the total sample size was calculated as 372 with 124 in each arm. Previous clinical trials in TBM have evaluated mortality as an outcome and considered 30% reduction [14]. Since we propose to evaluate composite outcome of death or disability, we have assumed a conservative effect size of 20% reduction. The 10% loss to follow-up is assumed based on the previous TBM trials as well as randomized controlled trials conducted at ICMR-NIRT, Chennai [20, 21].

### Data management

#### Data collection

Data which includes demographic, clinical, and laboratory information will be collected in case report forms (CRF). Data will be entered in the electronic data base after checking for completeness as per the detailed SOP and transmitted to the sponsor through a secure, web-based software system. The study site PI shall be responsible for the data quality and management. A central data management team will periodically review the quality of the data. An alphanumeric ID will be assigned to each participant to preserve personal information and contacts.

